## Abstract

**Background:**

Solid tumors, such as hepato-pancreato-biliary cancer, develop tumor hypoxia with tumor growth. Despite advances in surgery, a majority of these patients are in an unresectable condition. At this stage standard cytotoxic chemotherapy regimens are applied with limited success. Novel biological treatment options based on an antiangiogenic mechanism of action neglect other hypoxia mediated mechanisms (e.g. epithelial-mesenchymal transition, Warburg effect, and immunological response) leading to an increased invasiveness with a poor outcome.

The novel antihypoxic molecule myo-inositoltrispyrophosphate (ITPP, OXY111A) acts as an allosteric effector of hemoglobin and promotes normoxia in hypoxic tumors. In preclinical studies, tumor growth was reduced and survival prolonged. Additionally, a beneficial side effect profile was observed.

**Methods:**

In this first Ib/IIa clinical trial we will assess safety and tolerability of OXY111A as well as a proof of concept regarding efficacy in patients with non-resectable primary and secondary tumors of the liver, pancreas, and biliary tract. The study design is exploratory, prospective, open-labelled and mono-centric. The study is divided in a dose escalation part with a maximum of 48 subjects and an extension part, in which 21 subjects will be included.

**Discussion:**

The novel antihypoxic compound OXY111A has been tested in several cancer animal models showing beneficial effects for both survival and low side effect profiles. This first in patient application of OXY111A will reveal potential beneficial outcomes if anti-hypoxic therapy is added to standard cytotoxic treatment in patients with primary and secondary hepatopancreatobiliary tumors.

**Trial registration:**

Institution Ethical Board Approval ID: KEK-ZH-Nr. 2014-0374; Swiss regulatory authority Swissmedic (2015DR1009); ClinicalTrials.gov Identifier: NCT02528526, prospectively registered on November 11^th^, 2014.

## Background

Hypoxia occurs in almost any solid tumor beyond a certain size and it crucial for the development and progression of the disease [1]. The decreased oxygen partial pressure modifies tumor behavior. Best known is the increase in cancer-associated angiogenesis following hypoxia. Novel anti-cancer agents (e.g. bevacizumab) have been designed to specifically target the angiogenic response with the aim to starve the tumor. However, angiogenesis is only one part of the tumor's response towards hypoxia [2].

Molecularly, hypoxia leads to the stabilization of HIF (Hypoxia-Inducible Factors), transcription factors that regulate the response of cancer cells to tumor hypoxia. Apart from angiogenesis (e.g. via vascular endothelial growth factor, VEGF), HIFs promote a number of processes known to foster tumor development, including inflammation (e.g. via the NF-κB pathway), a shift to glycolysis (Warburg effect, e.g. via up-regulation of glucose transporter), invasive behavior (e.g. via Twist, an inducer of the epithelial-mesenchymal transition), and malignant potential (e.g. via OCT4 and other genes promoting a stem cell phenotype). Furthermore, HIFs have been implicated in the suppression of adaptive immunity and the protection from cell death. Importantly, the presence of hypoxia predicts a bad outcome for many tumor types, consistent with the observation promoting aggressive cancer behaviour (Fig. 1) [3]. Therefore, the prevention of hypoxia in the first place may provide an anticancer strategy superior to existing anti-angiogenic approaches [2, 4].

**Fig. 1 Fig1:**
[figure not shown]
Effects of hypoxia in HPB tumors

OXY111A is a synthetic allosteric effector of hemoglobin 4. OXY111A is taken up by red blood cells via the band 3.1 transporter and promotes the dissociation of oxygen from hemoglobin under conditions of low pO2. Thus, OXY111A increases the oxygen-releasing capacity of hemoglobin specifically under hypoxic conditions [5] and has the potential to prevent hypoxia without affecting the oxygen levels in the surrounding normoxic cells. OXY111A is the first anti-hypoxic compound without known, significant toxicities.

Thus far, OXY111A has been tested in five animal models of cancer [6–10]. In a syngeneic, orthotopic rat model of hepatocellular carcinoma, OXY111A prevented HIF1α stabilization as well as VEGF production and increased the apoptotic index, leading to a rapid reduction in tumor load along with dramatically improved survival in treated animals. Consistent with this finding, OXY111A treatment is generally associated with the inhibition of the hypoxic tumor response in all models studied [5–10]. The concept of vessel normalization through OXY111A has been impressively confirmed in a syngeneic rat model of pancreatic carcinoma and is of direct relevance to our patients [9]. Particularly important is the potentiation of chemotherapy, which is very likely a consequence to vessel normalization. Notably, no side effects were detected in all animal models, including those where OXY111A was shown to improve exercise capacity in healthy and sick mice [11].

The aim of this phase Ib/IIa clinical is to evaluate safety and tolerability of OXY111A in order to determine a maximum tolerated dose (MTD) as well as a proof of concept regarding efficacy in patients with primary or secondary malignancies of the liver, pancreas and biliary tract.

## Methods/Design

### Study design

This is a phase Ib/IIa dose escalation and extension study on the effects of OXY111A in patients suffering from primary and secondary hepato-pancreato-biliary or gastrointestinal malignancies not curable by surgical means.

The study design is exploratory, prospective, open-labelled and mono-centric. The study is divided in a dose escalation part with a maximum of 48 subjects and an extension part, in which 21 subjects will be included (specifically 4 dose expansion groups of 6 patients each determined by histology). Overall duration of an individual subject’s participation in the study is minimum 4 and maximum 9 weeks (Fig. 2).

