No more than 6 patients (3 + 3 patients) will receive the same dose during the dose escalation phase according to the following rules.Dose escalation to the subsequent cohort is possible if there is no DLT and no significant TET.If 1 DLT occurs, the ongoing cohort will be stopped, and another three patients will receive the next lower dose level tested, if only 3 patients have received this lower dose. If already 6 patients have received this lower dose, this lower dose represents MTD. If DLT occurs in cohort 1, the dose will be reduced to 4’200 mg/m^2^ weekly (ie. to 75 %), and this dose will be tested in 3 patients.If a 1-2 significant TETs occur, another three patients will receive the same dose.If out of 6 patients with the same dose, 3 or more significant TETs occur, this dose level will be the MTD.If out of 6 patients, 1-2 experience significant TETs, the dose may be increased to the next dose escalation step as shown in Table 1 in 3 additional patients. However, if a DLT has been observed, this dose must not be administered again.

Following these rules, a maximum of 48 patients are included in the dose escalation phase of the study. As soon as the MTD during the “dose escalation” phase is defined, a “dose extension” is performed in additional 21 subjects, who will receive the MTD.

In parallel, a maximum of three patients receiving the same dose of the IMP will be included in the study. Depending on the safety and tolerability of the compound, the next patient (or maximal the next three patients) who receives a higher dose, will be included after the last patient completed the whole IMP cycle (with a total of 9 applications) receiving the last lower dose.

A classical 3 + 3 phase I design was chosen for the dose escalation part of the study, because there is insufficient information on safety and tolerability of doses above 5’600 mg/m^2^ once weekly and of repeated doses in humans (unpublished data obtained from Normoxys®). This design induced the least toxicities in a simulation study comparing various dose finding escalation strategies and therefore appears to be most appropriate for a study using such substance in terminally ill cancer patients, where the therapeutic benefit is yet unknown.

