### Study population and number of patients

Patients with primary and secondary hepato-pancreato-biliary and gastrointestinal neoplasia will be assessed for eligibility at the interdisciplinary tumor board of the Swiss HPB Center. Patient information and informed consent will be obtained in the outpatient and inpatient hospital setting. Overall, a maximum of 69 patients will be included consisting of maximum of 48 in the dose escalation and 21 patients in the extension part of the study. OXY111A will be administered in an outpatient setting in the Phase I unit of the Clinical Trials Center of the University Hospital Zurich, in which the study equipment is reserved for this study explicitly. Appropriate back up material will be available in case of technical dysfunction. The study is planned to be completed within approximately two years.

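### The extension is given as 21 subjects but broken down as 4 groups of 6, which is 24; the overall maximum of 69 then conflicts with 72.

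*Protocol article*

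**What the plan says.** The protocol article gives the size of the extension in four places.

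- **Abstract, Methods:** "an extension part, in which 21 subjects will be included".
- **Study design:** the same number, followed by a breakdown: "an extension part, in which 21 subjects will be included (specifically 4 dose expansion groups of 6 patients each determined by histology".
- **Dose escalation and extension:** once the MTD is defined, "a “dose extension” is performed in additional 21 subjects, who will receive the MTD". The same section caps the escalation: "a maximum of 48 patients are included in the dose escalation phase of the study", with a limit per dose level: "No more than 6 patients (3 + 3 patients) will receive the same dose during the dose escalation phase".
- **Study population and number of patients:** "a maximum of 69 patients will be included consisting of maximum of 48 in the dose escalation and 21 patients in the extension part".

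The figure 21 therefore appears in all four places. The four histology groups of 6 appear only once, in the parenthesis under Study design.

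**The concern.** The parenthesis is introduced as a specification of the 21 subjects, so both figures describe the same people. Four groups of 6 are 24 people. The clash is within a single sentence of running prose; a broken table or condensation of a longer protocol does not explain it.

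The extension is the only part of the study organised by histology. If enrolment stops at 21, at least one histology group cannot reach its stated 6, and the article gives no rule for which. If all four groups are filled, the study exceeds its own stated maximum. That maximum is the enrolment ceiling of an open-label, early-phase study, so it should not be open to two readings.

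**Working it through.** **Inputs, all from the protocol article**

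- Dose levels: 8 (Table 1)
- Maximum per dose level in escalation: 6 (Dose escalation and extension)
- Escalation maximum: 48 (same section)
- Extension: 21 subjects; 4 groups of 6 (Study design)
- Overall maximum: 69 (Study population and number of patients)

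**Step 1. Reproduce the plan's own figures.**

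- Escalation: 8 × 6 = 48. Agrees.
- Overall: 48 + 21 = 69. Agrees.
- Extension from its breakdown: 4 × 6 = 24. Stated: 21. Does not agree; the difference is 3, and 3/24 = 12.5%.
- Overall maximum under the stated group structure: 48 + 24 = 72. Stated: 69.

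**Step 2. Look for an equal split that gives 21.** 21/4 = 5.25 and 21/6 = 3.5, neither a whole number. The equal splits of 21 into more than one group of more than one patient are 3 × 7 and 7 × 3. Neither has four groups or groups of six.

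**Step 3. Test whether escalation patients treated at the MTD could fill the gap.** If k of them counted towards the 24, the number still to enrol would be 24 − k.

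| Route under Dose escalation and extension | k | 24 − k | 21 + k |
|---|---|---|---|
| DLT at the next higher level; lower level already has 6 patients or is filled to 6 | 6 | 18 | 27 |
| 3 or more significant TETs among 6 patients at one level | 6 | 18 | 27 |
| Cohort 8 completed by 3 patients with no DLT and no significant TET | 3 | 21 | 24 |
| DLT in cohort 1, reduced dose then tested in 3 patients | 3 | 21 | 24 |

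Only k = 3 reconciles the figures, and it arises only on the last two routes, at the extremes of the dose range. A fixed 21 cannot rest on a count that depends on how the escalation ends.

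**Step 4. Illustrate what a short group would mean.** The article states no analysis by histology group, so this is only a gauge of precision. With 0 responders among n patients, the exact one-sided 95% upper bound for the response rate is 1 − 0.05^(1/n).

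- n = 6: 1 − 0.05^(1/6) = 0.393
- n = 5: 1 − 0.05^(1/5) = 0.451
- n = 3: 1 − 0.05^(1/3) = 0.632

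If the 3 missing patients are spread as 6/5/5/5 (sum 21), a short group has a bound of about 45% instead of 39%. If one group takes the whole shortfall, 6/6/6/3 (sum 21), its bound is about 63%.

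**The case against.** The best defence is that the totals are sound and only one parenthesis is off. 48 + 21 = 69 is correct, 21 is given consistently in four places, and the four groups of 6 occur once. That is true, and it locates the error: 69 fails only against the group structure. It does not remove the contradiction, and the weight of repetition does not prove which figure was meant.

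A second defence is that 3 escalation patients treated at the MTD count towards the 24. The arithmetic works on the two routes shown above, so the idea is not impossible. The text does not support it. Study design describes the 21 extension subjects themselves as the four groups, and the escalation section calls them additional. Nor are escalation patients described as chosen by histology, so nothing assigns 3 of them to a group.

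A third objection concerns weight. The design is expressly exploratory ("The study design is exploratory, prospective, open-labelled and mono-centric"), the primary outcome is safety and the MTD, and no power calculation is given for the extension. Three patients change no stated decision rule and no error rate. The article also ties proof of concept to the trial as a whole, not to the extension alone, and it sets out no responder analysis per group. All of this stands. The response-rate bounds are therefore illustrative, and the finding rests on the head count alone.

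**Conclusion.** The concern holds. The extension size is contradicted by its own breakdown: 21 against 4 × 6 = 24, a gap of 3 patients (12.5% of 24). The stated maximum of 69 correspondingly conflicts with 72. This conclusion needs no assumption beyond reading the parenthesis as a description of the 21 subjects, which is how the sentence is built. The effect on precision in a histology group depends on an allocation the article does not give: with 0 responders, the upper bound in a short group would be about 45% to 63%, against 39% with 6 patients. The documents do not settle whether 21 or four groups of 6 was intended. A maximum sample size that cannot be met together with the stated group sizes has to be corrected.

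**What to change.** Choose one of two corrections.

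1. **Keep 21 and 69.** Reword the parenthesis under Study design so that the groups sum to 21, for example up to 6 patients per histology group and 21 in total, with the planned group sizes given. This adds no enrolment and changes one sentence. The cost is that the stated groups become slightly smaller than 6 on average (21/4 = 5.25).
2. **Keep four groups of 6.** State 24 for the extension in the Abstract, Study design, Dose escalation and extension, and Study population and number of patients, and 72 for the overall maximum in the last of these. This raises the enrolment ceiling by 3.

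If patients from the escalation part are meant to count towards the histology groups, the article should say so, say how many, and drop the description of the extension subjects as additional or redefine it. The sponsor should confirm which figure stands in the full protocol.

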**Fig. 2 Fig2:**
[figure not shown]
Study flow chart

### Dose escalation and extension

The aim of the escalation study part is the assessment of additional preliminary safety and tolerability data for the MTD. Safety will be assessed according to the (Common Terminology Criteria for Adverse Events (CTCAE), also known as common toxicity criteria (CTC). These criteria are issued by the US National Cancer Institute for the standardized classification of adverse effects of drugs used in cancer therapy. Specific symptoms and conditions define each level of this classification system ranging from 1-5, where 1 is the mildest form of the specific symptom and 5 is death. The CTCAE version used for this study will be version 4.03.

According to CTCAE, Dose Limiting Toxicity (DLT) will be defined as:any grade 5 toxicityany grade 4 neutropenia lasting >7 daysany grade 3 febrile neutropenia, thrombocytopenia, or anemiaany grade 3 or 4 nonhematologic toxicity, excluding alopecia, that is considered by the investigator to be definitely, probably or possibly related to OXY111A.

A significant Treatment-Emergent Toxicity (TET) is defined as any other grade 2 toxicity considered by the investigator to be definitely, probably, or possibly related to OXY111A, but not fulfilling the criteria for DLT.

Based on the assessment of DLT and TET the MTD will be noted. MTD is defined as the dose preceding the dose level at which one patient in the cohort experiences a DLT during the treatment cycle, or the dose level at which 3 or more patients experience a significant TET.

There are two factors to be considered for the OXY111A dose escalation part of this study: total dose administered and infusion rate. The human equivalent dose-corrected No Observed Adverse Effect Level (NOAEL) in rats was 15’000 mg/m^2^ once a week for 5 weeks, while it was 43’750 mg/m^2^ in minipigs also once weekly (unpublished data obtained from Normoxys®). From animal studies, hypernatremia is known to be associated with high plasma concentrations typically encountered at the end of the OXY111A infusion and probably associated with infusion rate. Therefore, infusion rates of not more than 750 mg/m^2^/min are recommended. According to available phase I data in healthy volunteers (unpublished data obtained from Normoxys®), cohort 1 starts at a dose close to 5’600 mg/m^2^ weekly, i.e. 1866 mg/m^2^ thrice weekly. Dose escalation is performed according to the following scheme up to a maximum calculated dose of 43’700 mg/m^2^ weekly, which corresponds to the NOAEL level administered once weekly in minipigs.

Table 1 schedules dose escalation. In each cohort, 3 patients will be included (Table 1).

**Table 1 Tab1:** Dose escalation scheme

Cohort No.	Weekly Dose	Single Dose	Total Dose (9 applications )	% Dose Escalation
1	5'598 mg/m^2^	1'866 mg/m^2^	16'794 mg/m^2^	baseline
2	11'196 mg/m^2^	3’732 mg/m^2^	33'588 mg/m^2^	100 %
3	16'800 mg/m^2^	5‘600 mg/m^2^	50‘400 mg/m^2^	50 %
4	21‘000 mg/m^2^	7‘000 mg/m^2^	63‘000 mg/m^2^	25 %
5	26‘250 mg/m^2^	8‘750 mg/m^2^	78‘750 mg/m^2^	25 %
6	31‘500 mg/m^2^	10‘500 mg/m^2^	94‘500 mg/m^2^	20 %
7	37‘170 mg/m^2^	12'390 mg/m^2^	111‘510 mg/m^2^	18 %
8	43'500 mg/m^2^	14'500 mg/m^2^	130'500 mg/m^2^	~17 %

No more than 6 patients (3 + 3 patients) will receive the same dose during the dose escalation phase according to the following rules.Dose escalation to the subsequent cohort is possible if there is no DLT and no significant TET.If 1 DLT occurs, the ongoing cohort will be stopped, and another three patients will receive the next lower dose level tested, if only 3 patients have received this lower dose. If already 6 patients have received this lower dose, this lower dose represents MTD. If DLT occurs in cohort 1, the dose will be reduced to 4’200 mg/m^2^ weekly (ie. to 75 %), and this dose will be tested in 3 patients.If a 1-2 significant TETs occur, another three patients will receive the same dose.If out of 6 patients with the same dose, 3 or more significant TETs occur, this dose level will be the MTD.If out of 6 patients, 1-2 experience significant TETs, the dose may be increased to the next dose escalation step as shown in Table 1 in 3 additional patients. However, if a DLT has been observed, this dose must not be administered again.

Following these rules, a maximum of 48 patients are included in the dose escalation phase of the study. As soon as the MTD during the “dose escalation” phase is defined, a “dose extension” is performed in additional 21 subjects, who will receive the MTD.

In parallel, a maximum of three patients receiving the same dose of the IMP will be included in the study. Depending on the safety and tolerability of the compound, the next patient (or maximal the next three patients) who receives a higher dose, will be included after the last patient completed the whole IMP cycle (with a total of 9 applications) receiving the last lower dose.

A classical 3 + 3 phase I design was chosen for the dose escalation part of the study, because there is insufficient information on safety and tolerability of doses above 5’600 mg/m^2^ once weekly and of repeated doses in humans (unpublished data obtained from Normoxys®). This design induced the least toxicities in a simulation study comparing various dose finding escalation strategies and therefore appears to be most appropriate for a study using such substance in terminally ill cancer patients, where the therapeutic benefit is yet unknown.

The infusion rate must not be above 750 mg/m^2^/min. In order to achieve this, a constant infusion rate at 1/10 of the NOAEL infusion rate is chosen: an infusion rate of 75 mg/m^2^/min is scheduled for all dose steps. Due to the short half-life of OXY111A and the proposed mechanism of action, a slow, constant infusion over several hours appears more promising than a short infusion leading to excessively high concentrations of the compound.

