### Assessment of primary outcome

The primary outcome, safety and tolerability (establishing MTD) of the investigational medical product (IMP) will be assessed at every application for each patient. According to the 3 + 3 dose escalation schedule, after each patient, a decision on the continuation will be taken, i.e. to either add an additional patient in the same cohort or to continue with the next cohort after three patients.

Assessment will be done using CTCAE. The obtained data will be added to the electronic case report form (eCRF) using the software secuTrial® (interActive Systems GmbH (iAS), Berlin/Germany).

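### Some severe hematologic toxicities are neither DLT nor TET although a milder grade counts, so the written rules permit escalation after them

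*Protocol article*

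**What the plan says.** All definitions are in the protocol article under Dose escalation and extension. On grading: "The CTCAE version used for this study will be version 4.03".

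The DLT list has four items:
- any grade 5 toxicity;
- grade 4 neutropenia that lasts more than 7 days;
- febrile neutropenia, thrombocytopenia or anemia of grade 3, with no mention of grade 4;
- "grade 3 or 4 nonhematologic toxicity, excluding alopecia", if at least possibly related to OXY111A.

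A significant TET "is defined as any other grade 2 toxicity considered by the investigator to be definitely, probably, or possibly related to OXY111A", as long as it does not meet the DLT criteria. It has no *or higher*.

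These two classes drive the design. On the MTD: "Based on the assessment of DLT and TET the MTD will be noted". On moving up: "Dose escalation to the subsequent cohort is possible if there is no DLT and no significant TET". One DLT stops the cohort. If one or two "significant TETs occur, another three patients will receive the same dose". Three or more TETs among six patients make that dose the MTD.

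Two general provisions sit beside these rules. Opening of the next dose is qualified in the same section: "Depending on the safety and tolerability of the compound, the next patient" is included only after the last patient at the lower dose has completed the cycle. Under Assessment of primary outcome, "after each patient, a decision on the continuation will be taken".

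**The concern.** A toxicity scheme should never treat a worse event more leniently than a milder one of the same kind. This one does so in two places.

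**Neutropenia.** The DLT list takes only grade 4 lasting more than 7 days (and death), and TET takes only grade 2. Related grade 3 neutropenia and related grade 4 neutropenia of 7 days or less fall between them. Keeping short neutropenia out of DLT is a clinical choice and not at issue. The fault is that the TET definition does not then pick it up.

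**Thrombocytopenia, anemia and febrile neutropenia.** Grade 3 is a DLT. Read literally, grade 4 is not, and it cannot be a TET either.

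One patient with related grade 2 neutropenia obliges the team to treat three more patients at that dose. Three patients with related grade 3 neutropenia oblige it to do nothing, because the cohort has no DLT and no TET. The MTD is the primary outcome and the dose given to the 21 extension patients, so if such events occur it could be set too high. The article justifies the 3 + 3 design by how little is known about higher and repeated doses in humans, which makes the written rules an important safeguard.

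**Working it through.** **The plan's own figure.** Table 1 has 8 dose levels and at most 6 patients may receive each: 8 × 6 = 48, the stated maximum. This reproduces.

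**Classification.** Each toxicity named in the DLT list, assumed related to OXY111A, was set against the four DLT items and the TET sentence.

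| Related event | Grade 2 | Grade 3 | Grade 4 | Grade 5 |
|---|---|---|---|---|
| Neutropenia | TET | **neither** | DLT if over 7 days, otherwise **neither** | DLT |
| Febrile neutropenia | not enumerated | DLT | **neither** (literal) | DLT |
| Thrombocytopenia | TET | DLT | **neither** (literal) | DLT |
| Anemia | TET | DLT | **neither** (literal) | DLT |
| Nonhematologic | TET | DLT | DLT | DLT |

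Five event types are unclassified on the literal reading. If grade 3 in the third DLT item is read as a floor, the three grade 4 entries marked literal become DLTs and two remain, both neutropenia. With TET at grade 2 or higher and that DLT item at grade 3 or higher, none remains and no event already classified in the table changes class.

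**Size.** The article gives no hematologic event rates, so the per-patient rate p is assumed over a range. Further assumptions: patients are independent, no other DLT or TET occurs, and each episode is scored at its worst grade.

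*Neutropenia gap* (related grade 3 or short grade 4), with the corrected TET wording:
- Cohort held (expanded or declared MTD): P(at least 1 of 3) = 1 − (1 − p)³.
- Three more patients needed: P(1 or 2 of 3) = 1 − (1 − p)³ − p³. Expected extra patients are 3 times this.
- Dose becomes the MTD: p³ + 3p(1 − p)² × [3p²(1 − p) + p³] + 3p²(1 − p) × [1 − (1 − p)³]. The first term, three TETs in the first three patients, counts as MTD under the MTD definition; the other two reach three or more of six after expansion.

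At p = 0.2, for example: 0.008 + 0.384 × 0.104 + 0.096 × 0.488 = 0.095.

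| p | Held | P(1 or 2 of 3) | Extra patients | Becomes MTD |
|---|---|---|---|---|
| 0.1 | 0.271 | 0.270 | 0.81 | 0.015 |
| 0.2 | 0.488 | 0.480 | 1.44 | 0.095 |
| 0.3 | 0.657 | 0.630 | 1.89 | 0.246 |
| 0.5 | 0.875 | 0.750 | 2.25 | 0.641 |

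As written, these events contribute 0 to every column.

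*Grade 4 gap* (thrombocytopenia, anemia or febrile neutropenia). With the corrected DLT wording, a three-patient cohort shows at least one DLT with probability 1 − (1 − p)³ = 0.143, 0.271 and 0.488 at p = 0.05, 0.1 and 0.2. On the literal reading it is 0; on the floor reading there is no gap.

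**The case against.** Five points can be made in the plan's defense.

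1. *Grade 3 was surely meant as a floor.* Probably so; a team that must stop for grade 3 thrombocytopenia would hardly escalate after grade 4. But the next item in the same list spells out both grades, so the text itself points the other way. At most this closes the second gap. The neutropenia gap remains on either reading.
2. *Zero is too absolute.* The article does not say that only the worst grade of an episode counts. A count that passes through grade 2 on the way down or up could be scored as a TET, and one that passes through grade 3 thrombocytopenia as a DLT. This stands as a qualification: the zeros assume worst-grade scoring.
3. *The rates are speculative.* The only compound effect the article names is hypernatremia, it reports no side effects in the animal models, entry requires 28 days since chemotherapy, and a TET must be related to the drug. Rates of 30% or 50% are extreme. This also stands. The rule is wrong at any rate, but how often it would matter is unknown.
4. *The correction changes less than the held percentages suggest.* One or two TETs in six still allow escalation, and three or more make that same dose the MTD, not the one below. True: at 10%, 27% of cohorts are held but the dose becomes the MTD in only 1.5%.
5. *Judgment is built in.* Escalation is permitted, not forced, and the two general provisions leave room to pause. They name no event or grade, however. They cannot trigger the three extra patients or count toward the TETs that set the MTD.

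**Conclusion.** The concern holds. Related grade 3 neutropenia and related grade 4 neutropenia of 7 days or less are in neither class, whichever way grade 3 is read elsewhere, while related grade 2 neutropenia is a TET. Grade 4 thrombocytopenia, anemia and febrile neutropenia are a further gap on the literal reading only. Nonhematologic toxicity and grade 5 events are covered.

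The consequence is that escalation is permitted, not required, after these events, and that they do not count toward the MTD. The practical size depends on event rates that the article does not give and on worst-grade scoring; the 10% and 20% rows are the more plausible part of the range. This should be fixed, because it is a severity inversion in a stated rule that feeds the primary outcome. Confidence is high for neutropenia; for the grade 4 events it depends on how the item is read.

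**What to change.** Make two wording changes under Dose escalation and extension:
- In the third DLT item, replace *grade 3* with *grade 3 or higher*.
- In the TET definition, replace *grade 2* with *grade 2 or higher*, and keep the relatedness condition and the exclusion of events that are already DLTs.

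The 7-day threshold for neutropenia as a DLT can stay. It would also help to state that each episode is classified by its worst grade.

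The cost is a short amendment and possibly a few more expanded or stopped cohorts: about 0.8, 1.4 or 1.9 extra patients expected per dose level if related grade 3 or short grade 4 neutropenia occurs in 10%, 20% or 30% of patients. The maximum of 48 does not change, because it already allows six patients at each of the eight levels.

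### Three of the four DLT criteria do not require a link to OXY111A, so under the one-DLT stop a single clearly disease-caused event can cap the MTD

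*Protocol article*

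**What the plan says.** All of this stands in the protocol article under Dose escalation and extension.

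- **DLT criteria.** There are four: grade 5 toxicity; grade 4 neutropenia lasting more than 7 days; grade 3 febrile neutropenia, thrombocytopenia or anemia; and grade 3 or 4 "nonhematologic toxicity, excluding alopecia, that is considered by the investigator to be definitely, probably or possibly related to OXY111A". The causal clause appears only in the last.
- **Significant TET.** This definition carries a causal clause of its own: "any other grade 2 toxicity considered by the investigator to be definitely, probably, or possibly related to OXY111A".
- **MTD.** "MTD is defined as the dose preceding the dose level at which one patient in the cohort experiences a DLT during the treatment cycle".
- **Action on a DLT.** If "1 DLT occurs, the ongoing cohort will be stopped, and another three patients will receive the next lower dose level tested", provided only three have had that lower dose. If six have had it, it is the MTD. In addition, "if a DLT has been observed, this dose must not be administered again".
- **Use of the MTD.** The extension "is performed in additional 21 subjects, who will receive the MTD".
- **Design label and population.** "A classical 3 + 3 phase I design was chosen for the dose escalation part of the study", in part because the patients are "terminally ill cancer patients, where the therapeutic benefit is yet unknown".

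**The concern.** A one-DLT stop is a legitimate cautious rule. It has no tolerance for a stray event, so much depends on which events count. Here severe cytopenias count even when their cause is plainly the tumor, for example anemia from tumor bleeding. If grade 5 toxicity is read as any death, the result is also inconsistent: a tumor-caused grade 4 nonhematologic complication is not a DLT, but the same complication is one if it proves fatal.

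Nothing in the printed rules undoes such an event. The dose is not expanded and may not be given again. The MTD is the primary outcome and fixes the extension dose, so an event that says nothing about the drug could decide both.

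**Working it through.** **The plan's own figure.** 8 dose levels × 6 patients = 48, the stated escalation maximum.

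**Inputs from the document.** 8 levels; 3 patients per level, or 6 if expanded; stop at the first DLT; step down and fill the lower dose to 6. One cycle is 9 applications, three per week, so three weeks.

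**Assumed input.** b is the chance that a patient has an unrelated event meeting a DLT criterion during the cycle. The document gives no value. I use 1% and 2% and take b as the same at every dose, because such events do not depend on dose.

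**1. Drug with no related DLTs and no TETs: chance of stopping before all 8 levels are cleared**

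- As written, 24 patients must all be free of such events: 1 − (1 − b)^24.
  - b = 1%: 1 − 0.786 = 21%
  - b = 2%: 1 − 0.616 = 38%
- Classical 3+3, same criteria. A level is passed with 0 of 3, or with 1 of 3 followed by 0 of 3, so A = (1 − b)^3 + 3b(1 − b)^5, and the chance of stopping is 1 − A^8.
  - b = 1%: A = 0.9703 + 0.0285 = 0.9988, giving 1%
  - b = 2%: A = 0.9412 + 0.0542 = 0.9954, giving 4%
- As written, but with half of these events excluded as clearly unrelated (an assumed share): 1 − (1 − b/2)^24 = 11% and 21%.

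**2. Drug with related DLTs**

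Assumed related rates over levels 1 to 8: 2, 3, 5, 8, 12, 17, 25 and 33%, with no TETs. I simulated 100,000 trials per setting. Patients enter one at a time, the cohort stops at the first DLT, the trial steps down, and the lower dose is filled to 6. An MTD below cohort 1 is scored 0.

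| b | Mean MTD (level) | Trials whose first stop is an unrelated event | Related DLTs per trial |
|---|---|---|---|
| 0 (only related events count) | 3.55 | 0% | 1.27 |
| 1% | 3.22 | 12% | 1.12 |
| 2% | 2.93 | 22% | 1.01 |

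The loss is 3.55 − 3.22 = 0.33 of a level at 1%, and 3.55 − 2.93 = 0.62 at 2%.

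**3. Price of allowing attribution**

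Suppose 10% of true DLTs were wrongly dismissed. At a 20% DLT rate, the chance of stopping a 3-patient cohort falls from 1 − 0.80^3 = 49% to 1 − 0.82^3 = 45%.

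**The case against.** **The word toxicity may already imply drug causation.** The section presents CTCAE as a classification of adverse drug effects and defines DLT by reference to it, so grade 5 toxicity may mean a drug-caused death. This stands in part: a reader might infer that every tumor death is certainly a DLT, and the text does not settle that. It does not rescue the two blood-count criteria, which do not use the word. The nonhematologic criterion and the TET definition do use it and still add a causal clause, which would be redundant if the word were enough.

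**Counting regardless of cause may be deliberate caution.** Human data above 5,600 mg/m² weekly and on repeated dosing are sparse, and attribution in an open-label, single-center trial is subjective. This is a fair reason to keep the one-DLT rule and to count every doubtful event. It does not require counting an event whose cause is plainly something else, and the article does not say that this was intended.

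**The event rate is assumed.** This stands. Entry requires a life expectancy above 3 months, hemoglobin above 10 g/dL and adequate neutrophils and platelets, all of which select against early events. At 3% to 5% the first formula gives 52% to 71%, but nothing in the document supports rates that high, so they should carry little weight.

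**Most low dosing comes from the one-DLT rule itself.** This stands too. With only related events counted, the mean MTD is already just 3.55 of 8 levels under the assumed curve.

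**Conclusion.** The point holds as a flaw in the wording of the DLT definition, made consequential by the one-DLT stop. As written, one clearly disease-caused cytopenia caps the MTD and the extension dose. One disease-caused death does so too, if grade 5 toxicity is read as covering any death.

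The size rests on an assumed background rate of 1% to 2% per patient and cycle. It is a 21% to 38% chance of an unwarranted stop for a drug with no related DLTs. For a drug whose related DLT rates rise from 2% to 33%, it is a loss of about 0.3 to 0.6 of a dose level in the mean MTD.

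Three stronger readings are tempting but not supported:

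- **A whole level lost.** In the simulation the median MTD drops from cohort 4 to cohort 3, but it does so already at b = 0.5%, where the mean falls only from 3.55 to 3.39. The median sits on an edge and exaggerates the effect.
- **Efficacy tested at too low a dose.** The document gives no human dose-response data, so a lower MTD cannot be equated with an ineffective one.
- **Full removal by attribution.** A zero chance of an unwarranted stop needs perfect attribution. With unclear events still counted, the reduction is partial, as the 11% and 21% figures illustrate.

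This is a cheap and worthwhile improvement. It does not show that the design is unsound.

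**What to change.** Keep the one-DLT rule. In the DLT definition under Dose escalation and extension, add one sentence covering all four criteria: an event that meets a criterion counts as a DLT unless it is clearly and solely due to the underlying disease or another identified cause, and events of unclear cause count. In the same edit, the design could be called a modified, more conservative 3+3, since a classical one would expand after one DLT in three.

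How attribution is documented, and whether a patient lost to an unrelated event is replaced, are details the full protocol may already hold. They are not part of this point.

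The cost is one sentence and some reliance on judgement in an open-label trial. If 10% of true DLTs were dismissed, the cohort stopping chance at a 20% DLT rate would fall from 49% to 45%. Escalating further also exposes patients to slightly more related DLTs: from about 1.0 to at most 1.3 per trial at a 2% background, the upper figure applying if every unrelated event were excluded.
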